**Methods:**

Both intervention and control groups include 300 participants with low and 300 participants with high genetic risk for T2D. Genetic risk was evaluated by genetic risk score, and these two groups were matched additionally for fasting plasma glucose concentration, age, and body mass index. Corresponding control groups (300 participants each) do not have lifestyle intervention. The inclusion criteria are impaired fasting glucose at entry with or without impaired glucose tolerance, age 50–75 years, and body mass index ≥25 kg/m^2^. The primary outcome is incident T2D and the intervention lasts for 3 years.

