Several diabetes prevention trials have been published on the effects of lifestyle changes (diet and physical activity), and a meta-analysis of these trials reported a 57% reduction in incident T2D (8). There are no previous trials investigating the effect of the genetic background of the participants (the number of the risk alleles for T2D) on the effect of the prevention of T2D. Therefore, the aim of the T2D-GENE trial is to investigate the effects of lifestyle intervention (diet, physical activity, and weight maintenance/weight loss) on the prevention of incident T2D and the worsening of hyperglycemia in people with a high number of T2D risk alleles compared with people with a low number of T2D risk alleles. The second aim of our study is to investigate whether a group-based intervention utilizing a website is as effective as is an individual-based intervention. The hypotheses of the study are that lifestyle intervention is efficient independent of the number of T2D risk alleles (high and low genetic risks of T2D), and that a group-based intervention is as effective as an individual-based intervention in the prevention of T2D.

The primary outcome of our study is incident T2D defined by fasting plasma glucose ≥7.0 mmol/l or 2-h glucose ≥11.1 mmol/l in an oral glucose tolerance test (OGTT) or HbA1c ≥ 47 mmol/mol (6.5%), according to the American Diabetes Association criteria (9), or drug treatment for T2D started during a 3-year intervention trial. The secondary outcomes are changes in glucose area under the curve (AUC) in an OGTT, changes in insulin secretion and insulin sensitivity, and incident cardiovascular disease (CVD) events (fatal or non-fatal myocardial infarction, fatal or non-fatal stroke, death from cardiovascular causes or incident heart failure).

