## Participants and methods

### Participants

Study participants have been selected from the Metabolic Syndrome in Men (METSIM) study, which includes 10,197 men, aged from 45 to 73 years at baseline, randomly selected from the population register of the Kuopio town (baseline examination in 2005–2010) (10). The aim of the METSIM study is to investigate genetic and non-genetic factors associated with the risk of T2D, CVD, and insulin resistance-related traits.

The *inclusion criteria* for the present study were 1) IFG at entry (fasting plasma glucose 5.6–6.9 mmol/l) and with (2-h glucose 7.8–11.0 mmol/l) or without IGT (2-h glucose <7.8 mmol/l), and HbA1c <48 mmol/mol (<6.5%), 2) age 50–75 years, 3) body mass index (BMI) ≥25 kg/m^2^, and 4) the genetic risk score (GRS) (low risk 1–2 quintiles of the GRS and high risk 4–5 quintiles of the GRS). The *exclusion criteria* were 1) age <50 years or >75 years, 2) BMI <25 kg/m^2^, 3) type 1 or type 2 diabetes or isolated IGT (2-h plasma glucose <5.6 mmol/l and 2-h plasma glucose 7.8–11.0 mmol/l) or HbA1c ≥48 mmol/mol (≥6.5%), and 4) chronic diseases preventing to participate in the trial. After the identification of potential participants of the METSIM study, they were approached by an invitation letter.

The GRS in the present study was calculated on the basis of the number of risk alleles of 76 genetic variants increasing the risk for T2D as previously published (11). During the planning phase of the present study, less than 100 genetic variants increasing the risk for T2D had been published. A total of 600 participants were recruited and divided into two intervention groups (Fig. 1). Study participants, laboratory personnel, and clinical nutritionists were blinded with respect to the GRS of the participants throughout the study.

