**Fig. 1 F0001:**
[figure not shown]
Study design of the T2D-GENE trial. Participants in the intervention and control groups of the trial are divided into two groups based on the genetic risk score for type 2 diabetes (low genetic risk and high genetic risk). IFG, impaired fasting glucose; IGT, impaired glucose tolerance. The duration of the intervention is follow-up time is 3 years for all participants.

For both intervention groups (low GRS and high GRS), control groups of 300 participants (altogether 600 participants) of the METSIM study were selected and matched for GRS, fasting plasma glucose concentration, age, and BMI (Fig. 1). The rationale for these two control groups is to compare the incidence of T2D during the intervention between the two intervention groups and the two control groups.

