### Calculation of the sample size

The average proportion of participants in whom IGT progressed to T2D in the Finnish DPS study was 3%/year in the intervention group and 6%/year in the control group (4). The absolute incidence of T2D was 32 cases/1,000 person-years in the intervention group and 78/1,000 person-years in the control group (4). Using the results from the Finnish DPS study and assuming similar rates of incident T2D (6%/year) in the control group, a total of 69 individuals of 300 (our sample size) or 23% will develop diabetes during a 3-year intervention. The corresponding numbers in the intervention groups are 31 of 300 or 10%, indicating a 13% difference in incident T2D between these two groups. If α = 0.05 and β = 0.95, only 60 individuals/group are needed to demonstrate statistically significant difference between the intervention and control groups. Our group-based intervention might be less efficient than individual-based approach in the Finnish DPS study. If the effect of intervention is 6% (about half of the effect of that of the Finnish DPS study), then 267 participants are needed. Assuming around 10% of dropouts in this trial, a sample size of 300/each group has a power of 95% to demonstrate statistically significant reduction in incident T2D in the intervention groups compared with the control groups.

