### Statistical analyses

The primary analyses for the outcomes (incident T2D) in the time-to-event analyses will be based on a Cox proportional-hazards model with the study group (intervention and control) as a covariate in the low and high GRS groups. Linear regression will be used to evaluate the effect of intervention on insulin sensitivity, insulin secretion, the glucose AUC, and other continuous variables. Comparison between the study groups at baseline and at the end of 3-year intervention will be carried out with t-test (continuous variables) intervention and chi-square test (non-continuous variables).

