## Discussion

Our study will be the first study to compare the effect of lifestyle intervention on the prevention of incident T2D and the worsening of hyperglycemia in people with high genetic risk of T2D compared with people with low genetic risk of T2D.

If the effects of the lifestyle intervention are independent from the genetic risk of the participants, the implications of our study will be of great importance for the entire T2D research community, health care providers, and individuals at high risk for T2D. In this case, lifestyle intervention is beneficial for all individuals at risk for developing T2D, independently of genetic risk. If the effects of lifestyle intervention depend on the genetic risk, then individualized intervention programs are needed based on the GRS in people at high risk for T2D.

Due to the high number of people at risk for T2D in most countries, it will be challenging to organize individualized lifestyle counseling. In our study, lifestyle counseling is group-based, and a special website designed for this study is used for nutritionists-participant and participant-nutritionists contacts. From the resources point of view, it is important to examine whether a group-based intervention is effective similarly to a personal lifestyle counselling, and this study is likely to give an answer to this important question.

There are several previous lifestyle intervention studies, in counseling which the efficacy of lifestyle intervention on the prevention of T2D has been reported. Most of these studies have been performed in participants with IGT. In the present study, participants with IFG with or without IGT have been included. Most of the studies have combined diet and physical exercise, and a minority of the studies have only dietary intervention (17). In the systematic review and meta-analysis, the risk ratio (RR) was 0.68 (95% CI 0.5; 0.84) for dietary interventions and 0.59 (0.51; 0.69) for interventions combining diet and physical activity (17). In a more recent SRMA, the RR was 0.53 (0.41; 0.67) for interventions combining diet and physical activity (18).

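### The stated Cox analysis estimates the intervention effect within the low and high genetic-risk groups, but names no test comparing the two effects and leaves the quantitative allele score unused

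*Protocol article*

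**What the plan says.** - **Question.** The introduction of the protocol article states the hypothesis that "lifestyle intervention is efficient independent of the number of T2D risk alleles". The Discussion attaches consequences to either answer. Independence would mean benefit for everyone at risk; otherwise, "If the effects of lifestyle intervention depend on the genetic risk, then individualized intervention programs are needed based on the GRS".
- **Score.** Under Participants, the GRS is "calculated on the basis of the number of risk alleles of 76 genetic variants". Eligibility takes "low risk 1–2 quintiles of the GRS and high risk 4–5 quintiles of the GRS", so the middle fifth is left out.
- **Groups.** The abstract says "Both intervention and control groups include 300 participants with low and 300 participants with high genetic risk for T2D". The text under Fig. 1 says that controls were "matched for GRS, fasting plasma glucose concentration, age, and BMI".
- **Analysis.** Statistical analyses fits the primary Cox model "with the study group (intervention and control) as a covariate in the low and high GRS groups". This is the only use of the GRS stated there. No comparison of the two stratum effects is named, in grouped or continuous form.

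**The concern.** A hazard ratio in each stratum shows whether the intervention works in that stratum. It does not show whether the two effects differ. One may be significant and the other not when they are alike, and both may be significant when they differ. The central hypothesis concerns the difference, so the stated method stops one step short of it.

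A second issue is efficiency. A low/high label treats quintile 1 like quintile 2 and quintile 4 like quintile 5, although the hypothesis is worded by number of alleles and the score is known. If the effect changes gradually with the score, the label discards information that an interaction test needs. The hoped-for answer is no dependence, so an imprecise comparison leans towards it.

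**Working it through.** **The plan's own figures.** The article gives none for effect modification. Calculation of the sample size covers intervention versus control only ("If α = 0.05 and β = 0.95, only 60 individuals/group are needed"). That figure does not reproduce. With 23% vs 10%, two-sided α 0.05 and power 0.95:

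n = [1.96√(2×0.165×0.835) + 1.645√(0.23×0.77 + 0.10×0.90)]² / 0.13² = 1.879² / 0.0169 ≈ 209 per group.

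This is a separate matter. Only the rates are borrowed below, as illustration.

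**Information kept by low/high coding.** Assumptions, none given in the article: standard normal score X, even sampling within the retained quintiles, log hazard ratio linear in X.

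1. The cut is c = z(0.6) = 0.2533, with φ(c) = 0.3863.
2. E|X| = 2×0.3863/0.8 = 0.966.
3. E[X²] = (0.8 + 2×0.2533×0.3863)/0.8 = 1.245, with square root 1.116.
4. The correlation of the label with the score is 0.966/1.116 = 0.866. Its square is 0.749, so about 25% is lost.
5. Equal precision with the label needs 1/0.749 = 1.33 times the sample.

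**Sensitivity to score shape (modification still linear).**

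| Score | Kept | Lost |
|---|---|---|
| Uniform | 0.871 | 13% |
| Simulated 76-variant count (assumed allele frequencies) | 0.759 | 24% |
| Normal | 0.749 | 25% |
| Gamma, shape 4 | 0.704 | 30% |
| t, 5 df | 0.642 | 36% |
| Lognormal, log-SD 0.5 | 0.619 | 38% |

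**Sensitivity to the shape of modification.** Simulated 3-year event data, 1,200 participants, normal score:

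- Linear: the squared ratio of mean z statistics, grouped to continuous, was 0.751; power 48% grouped, 57% continuous.
- Step between low and high: the squared ratio was 1.336; power 42% grouped, 35% continuous. The advantage reverses.

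**What this means for power (linear, normal).** If δ is the noncentrality of the grouped interaction test, power with the continuous score is Φ(δ/√0.749 − 1.96). Grouped power of 50%, 60% and 80% becomes about 62%, 72% and 90%.

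**Illustration.** Assume 23% events in both control groups, 10% in the low-GRS intervention group and 17% (23% less 6 points) in the high-GRS intervention group, 300 each.

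- Low-GRS hazard ratio: ln 0.90/ln 0.77 = 0.403. High-GRS: ln 0.83/ln 0.77 = 0.713.
- Ratio 1.768, log 0.570.
- SE = √(1/69 + 1/30 + 1/69 + 1/51) = 0.286, so z = 1.99.
- Power: Φ(1.99 − 1.96) ≈ 51% grouped; Φ(1.99/0.866 − 1.96) ≈ 63% continuous.

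**Why non-significance is not independence.** With 23% vs 10% in both strata, the SE of the log ratio is √(2/69 + 2/30) = 0.309. An observed ratio of exactly 1 would have a 95% CI of exp(±1.96×0.309), that is 0.55 to 1.83. That interval still contains the ratio of 1.77 above.

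**The case against.** The strongest defence is that low versus high is the designed contrast. The abstract, introduction and Discussion word the aim as high-risk against low-risk people, and eligibility, the four groups of 300 and the sample size follow it. For that contrast a grouped analysis is the direct one, and a slope per allele answers a somewhat different question. This stands. The grouping is not an error, and the stratum hazard ratios should remain pre-specified estimates.

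A reader might infer that the analysis simply throws away a quarter of the information. The documents do not support that as an unconditional statement. They give neither the score's distribution nor the shape of any modification, and selection on glucose and BMI could alter the former. A reader might also infer that a continuous analysis is ruled out. It is not: the article is condensed, describes the primary analyses, and an unseen analysis plan could hold a supplementary one.

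What survives is narrower. The primary method stated for the central hypothesis contains no comparison of the two effects. The planned contrast of high with low needs one too, whatever coding is used.

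**Conclusion.** The point holds in conditional form. The more basic weakness is that no treatment-by-GRS comparison is stated; the coding of the score comes second. Low/high coding keeps about 75% of the interaction information if the score is approximately normal, sampling is even within the retained quintiles, and modification is linear on the log-hazard scale. Normality is reasonable for a sum over 76 variants, and a simulated count gives a 24% loss. Linearity is an assumption. Across the other score shapes tried, losses run from 13% to 38%, and under a step the grouped coding wins. The case for adding the continuous term is therefore that it uses available data and speaks to the hypothesis as worded by allele number, not that the grouped analysis is wrong.

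**What to change.** - Keep the low and high stratum hazard ratios as planned, and leave the recruitment strata unchanged.
- Add one Cox model of all participants with intervention, continuous GRS and their product. Report the product term with its 95% CI as the test of dependence on genetic risk.
- Report the intervention × low/high group interaction with its 95% CI alongside.
- Check the shape by comparing the two interaction codings. The relevant term is indicator × intervention. Adding the indicator alone examines only how the score predicts diabetes, not how it modifies the effect.
- State that independence will not be concluded from separate stratum results or from a non-significant interaction alone. The interval must be reported and discussed.

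**Cost.** Analysis wording only, since the score underlies eligibility and matching and so already exists. The downside is a linearity assumption that can be checked only weakly. The two codings correlate at about 0.87, so with both in one model the variance of each is inflated by about 1/(1 − 0.749) ≈ 4.

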## Methods

### Study visits

Participants in the intervention groups have four laboratory visits (0, 1, 2, and 3 years), and participants in the control groups have two laboratory visits (0 and 3 years) (Fig. 2). The study visits at 0 and 3 years include a questionnaire on physical activity at work and leisure time, smoking, alcohol use, history of diseases, and current medication, and dietary habits (food frequency questionnaire), blood pressure (three measurements 1 min apart), body weight, height, and bioimpedance for measure fat percentage. Laboratory measurements include an OGTT (plasma glucose and insulin concentrations at 0, 30, and 120 min), HbA1c, and concentrations of total LDL and HDL cholesterol, total triglycerides, alanine aminotransferase, creatinine, interleukin 1 receptor antagonist, and high sensitivity C-reactive protein. The three-factor eating questionnaire R18 (TFEQ-R18) (12) is used for the evaluation of participants’ eating behavior (cognitive restraint, uncontrolled eating, and emotional eating) during the intervention. In the intervention group, the 1-year visit includes measurement of non-fasting HbA1c. At the 2-year visit, the TFEQ-R18 questionnaire is filled, and body weight, blood pressure, and the laboratory measurements are performed similarly as at 0-year and 3-year visits.

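### The plan names both a linear regression and an unadjusted year-3 t-test for the same continuous outcomes, without saying which gives the intervention effect in this matched, non-randomised comparison

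*Protocol article*

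**What the plan says.** The Statistical analyses section of the Protocol article gives two methods for continuous variables in consecutive sentences.

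- Regression: "Linear regression will be used to evaluate the effect of intervention on insulin sensitivity, insulin secretion, the glucose AUC, and other continuous variables". Neither the response (year-3 value or change) nor any covariate is stated.
- t-test: "Comparison between the study groups at baseline and at the end of 3-year intervention will be carried out with t-test (continuous variables". Non-continuous variables get a chi-square test in the same sentence.

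Three other places bear on this.

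- Introduction, paragraph on outcomes: "The secondary outcomes are changes in glucose area under the curve (AUC) in an OGTT, changes in insulin secretion and insulin sensitivity".
- Participants, text under Fig. 1: "control groups of 300 participants (altogether 600 participants) of the METSIM study were selected and matched for GRS, fasting plasma glucose concentration, age, and BMI". No random allocation between intervention and control is described.
- Study visits: "Participants in the intervention groups have four laboratory visits (0, 1, 2, and 3 years", while "participants in the control groups have two laboratory visits (0 and 3 years". The year-0 and year-3 visits include an OGTT with glucose and insulin, so the baseline value of each secondary metabolic outcome exists in both groups.

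**The concern.** Two t-tests, one at year 0 and one at year 3, estimate two cross-sectional differences. Neither tests whether the groups changed differently, which is what the secondary outcomes ask. In a randomised trial the year-3 contrast would at least be unbiased, if inefficient. Here the controls were chosen from the cohort and matched on genetic risk score (GRS), fasting glucose, age and BMI. They were not matched directly on glucose AUC, the Matsuda index or the disposition index. A difference present at entry could therefore reappear at year 3 and be read as an effect.

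The regression sentence does not settle the matter. If the response is the year-3 value and group is the only term, the regression reproduces the equal-variance t-test. Because neither method is ranked above the other, the analyst may choose between two answers after seeing them. Only the continuous outcomes are at stake; the Cox analysis of incident diabetes is not affected.

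**Working it through.** The article gives no SD, correlation or power for any continuous outcome, so there is no stated figure to reproduce. The check shows what an unadjusted year-3 comparison would cost if it were used for inference.

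**Inputs**

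- Group size 300 less about 10% dropout (Calculation of the sample size) = 270 per group, for one intervention-control pair.
- α = 0.05 (same section); two-sided is assumed.
- r, the within-group correlation of baseline and year-3 value: assumed, 0.3 to 0.8.
- b, the residual baseline imbalance: assumed, 0.1 to 0.2 SD.
- Equal SDs at baseline and year 3, set to 1.

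**Precision**

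Relative to the year-3 t-test, the variance of the group difference is 1 − r² with baseline adjustment and 2(1 − r) for change scores. The t-test has 80% power at an effect of (1.960 + 0.842) × √(2/270) = 0.241 SD. At that effect:

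| r | Adjusted variance, 1 − r² | t-test relative to adjusted, 1/(1 − r²) | Change-score variance, 2(1 − r) | Power, adjusted | Power, change score |
|---|---|---|---|---|---|
| 0.3 | 0.91 | 1.10 | 1.40 | 83.6% | 65.8% |
| 0.5 | 0.75 | 1.33 | 1.00 | 89.9% | 80.0% |
| 0.7 | 0.51 | 1.96 | 0.60 | 97.5% | 95.1% |
| 0.8 | 0.36 | 2.78 | 0.40 | 99.7% | 99.3% |

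**Bias**

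Suppose the intervention has no effect and the year-3 value depends on baseline with slope r. An imbalance b then appears as r × b in the year-3 difference. The standard error is √(2/270) = 0.086 SD, which gives the true false-positive rate of a nominal 5% t-test:

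| r | b = 0.1 SD: bias, false-positive rate | b = 0.2 SD: bias, false-positive rate |
|---|---|---|
| 0.3 | 0.03 SD, 6.4% | 0.06 SD, 10.7% |
| 0.5 | 0.05 SD, 8.9% | 0.10 SD, 21.3% |
| 0.7 | 0.07 SD, 12.9% | 0.14 SD, 37.0% |
| 0.8 | 0.08 SD, 15.3% | 0.16 SD, 46.0% |

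**Limit of the adjusted analysis**

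Without randomisation, baseline adjustment also rests on an assumption. If an untreated baseline gap would persist in full and not shrink by the factor r, adjustment leaves (1 − r) × b. With b = 0.2 SD this is 0.10 SD at r = 0.5 and 0.06 SD at r = 0.7. A change score is unbiased in that case, and the t-test carries all of b. If the gap shrinks by the factor r, the change score is off by (1 − r) × b in the opposite direction and the adjusted analysis is unbiased. In neither case is the year-3 t-test unbiased.

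**The case against.** The strongest reply is that the article does name an effect analysis, and it is regression. The t-test sentence refers to comparing groups at two time points and pairs the test with chi-square, so it may well be meant as description. A reader might infer from that sentence alone that the t-test is the planned effect analysis, and so that precision is lost and bias is built in. The documents do not support that reading. They also nowhere say that an effect will be inferred from no significant difference at entry followed by one at year 3.

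Two further points stand. A missing covariate list is detail that a protocol article commonly leaves to a fuller document, so it is no finding by itself. Matching also does real work: fasting glucose is one of the three OGTT glucose points, so matching on it bears directly on glucose AUC. The imbalance left after matching may be small, and b above is assumed.

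The objection does not remove the t-test that is actually written down. The text plans it for the same variables, gives it no descriptive label and does not place it below the regression. Defining the outcomes as changes suggests a change-score or baseline-adjusted regression, but the Statistical analyses section does not say so.

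**Conclusion.** The point holds as a lack of hierarchy between two stated methods, one of which does not suit the outcomes or the design. If the year-3 t-test, or a regression of the year-3 value on group alone, were used for inference, its variance would be 1.3 to 2.0 times that of the baseline-adjusted analysis for an assumed r of 0.5 to 0.7. It would also carry about r × b of bias: 0.03 to 0.16 SD over r = 0.3 to 0.8 and b = 0.1 to 0.2 SD. None of these correlations or imbalances comes from the documents, and the figures do not apply if the reported effect comes from a regression that uses the baseline value. The point concerns secondary and other continuous outcomes only. It should be corrected because the written method is weaker than one the collected data already allow.

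**What to change.** State in the Statistical analyses section, and in the analysis plan, that:

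- the intervention effect on glucose AUC, Matsuda index, disposition index and other continuous outcomes is the study-group coefficient from linear regression of the year-3 value on study group, the baseline value of that outcome, and the matching factors (GRS group, fasting glucose, age, BMI);
- a change-score analysis is a sensitivity analysis, because allocation was not randomised and the two approaches assume different things about how a baseline gap would evolve untreated;
- the t-tests are descriptive, and no effect is inferred from the year-3 t-test.

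The cost is a change of wording and one extra sensitivity analysis. No new data are needed, since both groups have year-0 and year-3 OGTT measurements.
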